### Sample size {14}

To ensure sufficient power for the effects at all time points, we considered potential dropout and power analysis for the last follow-up time point after 6 months (T3) using G*power. Dropout for patients with a depressive disorder in IBIs over the course of 6 months was estimated to be 50% based on previous literature [53]. For smartphone-based interventions targeting depressive symptoms, meta-analyses found small (*g* = 0.28, [54]) to small-to-moderate (*g* = 0.383, [55]) effect sizes when comparing apps to control conditions. As the TAU group in our study must be considered an informed TAU group due to the screening process, the calculation of our sample size is conservatively based on a small effect size (*d* = 0.3). The sample size calculation is conservatively based on a small effect size (*d* = 0.3), as the TAU group must be considered an informed TAU group due to the screening process. To find this effect in a randomized controlled trial with a one-tailed *t*-test (alpha error level = 5%, power = 0.80) for independent samples, *n* = 139 participants per treatment group (total *n* = 278 participants) are needed to complete the t3 assessment. Considering the dropout rate, a total sample of *N* = 556 participants is needed at the time of randomization (1:1 randomization: *n* = 278 participants in IG; *n* = 278 participants in TAU).

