## Statistical methods

### Statistical methods for primary and secondary outcomes {20a}

It is possible that some participants may not utilize the app, despite being assigned to the intervention group, and yet still participate in the surveys (non-compliance). We will deal with non-compliance in the analyses in two different ways. For the primary analyses, we will include data from all randomized patients and evaluate both (1) the effect of assignment to the intervention and (2) the effect of the intervention itself. For the estimation of the causal effect of the assignment to intervention on the primary and secondary endpoints (intention-to-treat analysis), the mean values between the two study groups at T1, T2, and T3 will be compared using *t*-tests and MANOVAs within the framework of structural equation models (SEM). For estimating the causal effect of the intervention itself on the primary and secondary endpoints, we treat all participants who were assigned to the intervention group but did not use the app (and did not drop out before the measurement of the first endpoint) as members of the control group (as-treated analysis). As this invalidates randomization, we will control for selection bias by adding the variables measured at baseline as covariates in the model. We assess all endpoints also at baseline, as this helps to assure the ignorability assumption (e.g., Cook, Steiner, & Pohl, 2010). Assumptions on distribution and homoscedasticity are tested and, if violated, relaxed (by using respective estimators or multi-group modeling).

To investigate the utilization of care services, means on individual items of the FIMPsy will be compared between the two treatment groups via *t*-tests in SEM.

For the intervention group, usability and acceptance of the intervention are analyzed using descriptive statistics to describe satisfaction (CSQ-i, SUS) and utilization behavior. The different recruitment channels for the intervention are surveyed and descriptively analyzed.

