### Methods for additional analyses (e.g., subgroup analyses) {20b}

#### Differential effects

We will evaluate whether the intervention effect differs between subgroups in a moderator analysis. For this, we will include the variables measured at baseline as further independent variables in the analysis model and evaluate their two-way interaction with the intervention variable on the endpoints (e.g., age, childbirth-related trauma, history of depressive episodes, number of children, income, subjective socioeconomic status, pregnancy complications, birth complications, mode of delivery, pregnancy intention, health care utilization, and level of education).

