### Methods in analysis to handle protocol non-adherence and any statistical methods to handle missing data {20c}

#### Dropout

To deal with missing data due to dropout, analyses are conducted in the context of structural equation modeling and estimated by full information maximum likelihood using all variables measured at baseline as auxiliary variables.

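### Arm-specific modelling of the ITT effect depends on a preliminary variance test, so FIML under heavy dropout can bias the group difference if one baseline variable both predicts dropout and modifies the effect

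*Protocol article*

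**What the plan says.** Under Statistical methods {20a}, the protocol estimates the effect of assignment in all randomised women by comparing arm means at T1, T2 and T3 with t-tests and MANOVAs inside an SEM. On model assumptions it states: "Assumptions on distribution and homoscedasticity are tested and, if violated, relaxed (by using respective estimators or multi-group modeling"). Multi-group modelling is one of two remedies, and both apply only after a failed test.

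Under Dropout in {20c}, the analyses are "estimated by full information maximum likelihood using all variables measured at baseline as auxiliary variables". Under Sample size {14}, dropout "over the course of 6 months was estimated to be 50% based on previous literature". That figure is for t3. No figure is given for t1, which the Outcomes section treats as the most relevant time point. Under Differential effects {20b}, baseline variables enter an additional analysis to "evaluate their two-way interaction with the intervention variable on the endpoints". Those interactions are not part of the ITT model.

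**The concern.** If separate parameters for the arms are a relaxation, the starting model shares its covariance parameters between the arms. FIML then recovers the mean of the women who dropped out by using one slope of outcome on each baseline variable for both arms.

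Suppose the intervention helps more, or less, at higher baseline values. The slopes then differ by arm. If the same baseline variable also drives dropout, the common slope is wrong in each arm exactly where the data are missing. The estimate drifts from the effect in all randomised women towards the effect in those who stayed. This happens although the data are missing at random and the right auxiliary variables are in the model.

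The trigger looks elsewhere. A homoscedasticity test compares variances, and two arms can have equal variances with unequal slopes. The other remedy, a different estimator such as robust standard errors, changes the standard error but leaves this bias in place even when the test rejects.

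**Working it through.** **The plan's own figure.** Inputs from Sample size {14}: d = 0.3, one-tailed 5%, power 0.80, 50% dropout. n per arm = 2(1.645 + 0.842)²/0.3² = 137.4, so 138. The noncentral t gives 138.07, rounded up to 139. Then 2 × 139/0.5 = 556. The stated sample size reproduces and is not in question.

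**Assumptions (not in the protocol).** One standardised baseline variable x; baseline-outcome slopes b_TAU and b_IG; a logistic dropout model with a given odds ratio per SD of x and 50% dropout overall; true difference (IG minus TAU) -0.30 SD; 278 per arm.

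**Bias of the pooled model.** For arm i, let Δ_i be the mean of x in all randomised women minus its mean in completers, and let b be the common slope. The error in the arm mean is (b - b_i)Δ_i. With the same Δ in both arms, the error in the difference is

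bias = (b_TAU - b_IG) × Δ.

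With 50% dropout, Δ = -2·E[x/(1 + exp(gx))], where g is the log odds ratio. This gives Δ = 0.195 for an odds ratio of 1.5 and 0.3125 for 2.

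| Slopes TAU / IG | Odds ratio per SD | Bias | Pooled estimate |
|---|---|---|---|
| 0.50 / 0.35 | 1.5 | 0.15 × 0.195 = +0.029 | -0.27 |
| 0.65 / 0.35 | 1.5 | 0.30 × 0.195 = +0.059 | -0.24 |
| 0.65 / 0.45 | 2 | 0.20 × 0.3125 = +0.063 | -0.24 |
| 0.65 / 0.35 | 2 | 0.30 × 0.3125 = +0.094 | -0.21 |
| 0.40 / 0.65 | 2 | -0.25 × 0.3125 = -0.078 | -0.38 |

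**Simulation (4000 trials per scenario).** With slopes 0.5/0.2 and completer shifts of -0.24, -0.35 and -0.47 SD, the pooled bias was +0.067, +0.103 and +0.138. The formula gives 0.072, 0.105 and 0.141. The arm-specific model stayed within 0.004 of the truth in every scenario.

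**When the bias vanishes.**
- Slopes 0.5/0.2, dropout unrelated to x: -0.001.
- Equal slopes, dropout related to x: -0.003.
- Slopes 0.5/0.2, dropout in opposite directions in the two arms: +0.004, because the errors cancel.
- Slopes 0.5/0.2, dropout related to x in one arm only: about half the bias remains (+0.056 and +0.057).

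**The test as gate.** In the three scenarios with bias +0.067, +0.103 and +0.138, a Levene test at 5% rejected in 21%, 22% and 18% of trials. Even if every rejection led to the two-group model, +0.049, +0.076 and +0.107 remained. With equal total variances the test rejected in 5% of trials, and +0.103 of +0.107 remained.

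**Effect on power.** With 139 completers per arm and a one-sided 5% test, a true 0.3 gives power of about 80%. If a bias of 0.10 SD shrinks it to 0.2, power is about 51%.

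**The case against.** The strongest reply is that the protocol never says outright that the covariances are pooled. How an SEM is parameterised is commonly left to the analysis plan. This stands in part: the pooled default is an inference, though the natural one when multi-group modelling appears only as a relaxation. What the text does fix is the test-then-relax rule, and that rule is the target here. For a MANOVA, homoscedasticity might be read as equality of the endpoint covariance matrices, but that still leaves out the slopes of endpoints on baseline.

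A reader might infer that the estimate is biased whenever benefit depends on baseline, or that 50% dropout alone biases it. Neither follows: the same variable must also drive dropout, without cancellation between the arms. A reader might also infer that the plan expects moderation. {20b} says only that it will be examined, and its examples do not name baseline EPDS. Finally, the 50% must not be carried over to t1. With less selective loss there, the bias would be smaller.

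The size is also open to challenge. With slopes 0.5/0.4 and odds ratios of about 1.2 to 1.5, the pooled estimate is -0.29 to -0.28. In such mild cases the root mean squared error of the two models is practically the same (0.112-0.120 against 0.114-0.119). Material bias needs the larger contrasts.

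**Conclusion.** The concern holds in conditional form. The rule in {20a} makes arm-specific modelling depend on a test that does not address the assumption that matters for FIML here and has little power to detect its failure. The resulting bias at t3 ranges from none, through about 0.03 SD for a mild contrast, to about 0.09 SD for a strong one, against a planned 0.30. It can go in either direction. These sizes rest on assumed slopes and on an assumed dependence of dropout on baseline, neither of which the protocol gives. They also rest on reading the default as a common-covariance model. Confidence is medium. The change is worth making because it is cheap and because it takes a data-dependent model choice out of the primary analysis.

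**What to change.** In {20a} and {20c}, state that the ITT SEM is fitted as a two-group model from the outset: means, variances and baseline-outcome covariances estimated separately in IG and TAU, FIML within that model, robust standard errors, and the difference in model-implied means as the effect. Remove the preliminary test as the trigger for multi-group modelling.

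Name the arm-specific auxiliary variables in advance. They should include at least the baseline values of the endpoints, plus those prespecified moderators thought to predict dropout. Do not let the set depend on whether the model converges, since that would bring back a choice made on the data.

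Cost: analysis wording only, with no new data and no change to the 556. If there is no moderation, the standard error rises by about 2-9%, depending on the number of auxiliaries. In one check at t3, the SD of the estimate went from 0.112 to 0.118, which is 0.006/0.112, or about 5%.

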### Interim analyses {21b}

N/a: No interim analysis is planned in this trial.

### Methods for additional analyses (e.g., subgroup analyses) {20b}

#### Differential effects

We will evaluate whether the intervention effect differs between subgroups in a moderator analysis. For this, we will include the variables measured at baseline as further independent variables in the analysis model and evaluate their two-way interaction with the intervention variable on the endpoints (e.g., age, childbirth-related trauma, history of depressive episodes, number of children, income, subjective socioeconomic status, pregnancy complications, birth complications, mode of delivery, pregnancy intention, health care utilization, and level of education).

#### Extensity of app use

In additional analyses, we will explore which aspects are related to the extensity of app use. For this, we will only consider the data of the intervention group to explore in which way the number of modules taken related to the endpoints, we will regress the endpoint variables to the number of modules taken in a SEM framework. As the number of modules is not randomized, we will furthermore control for covariates (e.g., sickness, chronic illnesses of household members, working hours, number of children).

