**Methods:**

We will conduct a two-arm randomized controlled trial to assess the effectiveness of a smartphone-based intervention in comparison to a treatment-as-usual control group in Germany. Our aim is to randomize 556 participants in a 1:1 ratio. Participants in the intervention group will be provided access to a preventive smartphone-based intervention called “Smart-e-Moms,” which incorporates therapeutic support and comprises 10 concise modules rooted in cognitive-behavioral therapy. For the intervention group, evaluations will take place at baseline (t0), prior to sessions 4 and 8 (intermediate assessments), and upon completing the intervention 6 weeks after baseline (t1). The control group’s assessments will be at baseline (t0) and 6 weeks after baseline. Follow-up assessments are scheduled at 12 and 24 weeks from baseline to examine the short-term stability of any observed effects. We anticipate that participants in the intervention group will exhibit improvements in their postpartum depressive symptoms (as measured with the Edinburgh Postnatal Depression Scale). Additionally, we will analyze secondary outcomes, including maternal bonding, stress levels, self-efficacy, satisfaction with the intervention, and healthcare utilization.

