### Intervention description {11a}

Smart-e-Moms is a therapist-guided smartphone-based intervention to reduce symptoms of postpartum depression in mothers. The intervention will be delivered on the DIRECT app developed by Freie Universität Berlin. At the beginning of the intervention, each participant will be assigned to a therapist who guides the participant through the intervention and provides written, individualized feedback at several time points. Smart-e-Moms consists of 10 sessions (see Table 1 for a description of the intervention components) that are delivered to the participants over the course of 5 weeks (i.e., 2 sessions/week). Every session lasts about 20 min and consists of psychoeducational content, interactive exercises, and summaries of the modules. The sessions are presented sequentially to the participants, with individualized feedback and encouragement given by the therapist after sessions 1, 3, 5, 7, 9, and 10. Additional information on topics related to postpartum mental health (i.e., depression and breastfeeding, child development) will be available throughout the intervention. Furthermore, throughout the intervention, participants will gain access to several additional tools, including a mood tracker, an activity planner, relaxation exercises, exercises for strengthening maternal bonding, and a pinboard to collect moments of happiness.

**Table 1 Tab1:** Intervention components

Session number	Session name	Main topics	Key interventions	Session goal
1	Welcome session	Introduction of the intervention and individual goal setting, psychoeducation about PPD	Mood tracker^a^, expressive writing	Increasing the awareness of one’s own symptoms and normalizing negative emotions, establishing program motivation
Individualized written feedback provided by a psychologist				
2 + 3	Myths about motherhood	Myths about motherhood, association between thoughts and feelings	Collection of happy moments^a^, expressive writing	Debunking myths about motherhood through cognitive restructuring, reducing feelings of shame, increasing one’s focus on moments of happiness
Individualized written feedback provided by a psychologist				
4 + 5	Establishing soothing activities	Link between soothing activities and mood, dealing with challenges	Activity planner^a^, expressive writing	Behavioral activation and implementation of soothing activities—appropriate for the postpartum period—into everyday life with child

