### Criteria for discontinuing or modifying allocated interventions {11b}

Participants can leave the study at any time for any reason if they wish to do so without any consequences.

Engagement in the program (i.e., starting and/or completion of sessions) will be automatically logged. After 1 week without starting or completing a new session, participants will receive a reminder message. Participants will still be invited to fill out all assessments even if they discontinue working on the sessions.

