## Data collection and management

### Plans for assessment and collection of outcomes {18a}

Our study focuses on postpartum depressive symptoms as the primary outcome, with secondary measures including mother–child bonding, self-efficacy, stress, app quality, and healthcare utilization. Other measures encompass sociodemographic, clinical, and pregnancy-related variables. Outcomes will be measured by self-reported questionnaires, which are assessed at baseline (t0), after completion of the intervention 6 weeks after allocation (IG) or 6 weeks after allocation (TAU) (t1), and at 12 weeks (t2) and 6 months (t3) after allocation. Participants who receive the intervention will also complete an intermediate assessment before session 4 (t0_1) and session 8 (t0_2). All questionnaires will be presented via the DIRECT app that also hosts the intervention. A detailed overview of all assessments can be found in Table 2.

**Table 2 Tab2:** Schedule of enrolment, interventions, and assessments

**Time point**		**Study period**							
		**Enrollment**	**Baseline**	**Allocation**	**Post-allocation**				
		(− t1)	(t0)	(0)	(t0_1) Session 4, ~ week 2	(t0_2) Session 8, ~ week 4	(t1) After completion, ~ week 6	(t2) Follow-up, week 12	(t3) Follow-up, week 24

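### The exploratory regression of endpoints on self-selected module count names no baseline or early symptom score, so its slope can differ from zero when sessions do nothing

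*Protocol article*

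**What the plan says.** The section on extensity of app use, among the additional analyses {20b}, restricts this analysis to one arm: "we will only consider the data of the intervention group". The model is a regression: "we will regress the endpoint variables to the number of modules taken in a SEM framework". The protocol recognises the selection problem and gives its remedy: "As the number of modules is not randomized, we will furthermore control for covariates". The examples that follow are sickness, chronic illness in the household, working hours and number of children.

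Four other places bear on this:
- **Dose.** The abstract says that the programme "comprises 10 concise modules rooted in cognitive-behavioral therapy". The intervention description {11a} has 10 sessions "delivered to the participants over the course of 5 weeks (i.e., 2 sessions/week").
- **Stopping.** Section {11b}: "Participants will still be invited to fill out all assessments even if they discontinue working on the sessions". A low module count can therefore be paired with an observed endpoint.
- **Early course.** Section {18a}: "Participants who receive the intervention will also complete an intermediate assessment before session 4 (t0_1) and session 8 (t0_2"). Table 2 marks EPDS and stress at both of these points, and PATHEV at baseline.
- **Other analyses.** In the as-treated analysis {20a}, baseline variables enter as covariates to control selection bias. In the dropout paragraph {20c}, baseline variables serve as auxiliaries for full information maximum likelihood (FIML).

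**The concern.** There is no randomised contrast inside the intervention group. The exposure builds up over several weeks, and a woman's decision to go on may depend on her symptoms so far. If it does, early course influences both the module count and the later EPDS. A regression on the total count then attributes to the modules what belongs to the course.

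The bias can go either way. If women who get worse stop, the slope suggests benefit per module. If women who get better stop because they no longer need the programme, it suggests harm.

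The named examples do not address this, because none is a symptom score. The FIML auxiliaries do not address it either: they support the missing-data assumption and do not adjust the slope. The intermediate EPDS and stress scores would help most, but no analysis in the statistical methods uses them. At stake is how the only planned analysis of graded programme use can be read. The as-treated analysis separates only users from non-users.

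**Working it through.** **The plan's own figures.** The article gives no figure for this analysis. Its sample size supplies the group sizes used below. With d = 0.3, one-tailed alpha 5% and power 80%, the exact noncentral t calculation gives 139 per group (power 0.802), as stated. Then 278 / (1 − 0.5) = 556, also as stated. The intervention group is thus 278 at randomisation and 139 expected at t3.

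**Calculation A: stopping depends on measured early change.** No session has any effect. The following are assumptions and are not in the article:
- Standardised scores: baseline b ~ N(0,1); session-4 score e = r·b + √(1−r²)·ε₁; final score y = r·e + √(1−r²)·ε₂; r = 0.5 or 0.7. Final EPDS is 5·y, so its SD is 5. The eligibility cutoff is not modelled.
- Early worsening: c = (e − r·b)/√(1−r²).
- Log-odds of doing the next session: 2.2 + 0.15·(sum of four independent covariates), which is about 90% at the mean. From session 4 on, g·c is subtracted.
- g > 0 means that worsening women stop; g < 0 means that improving women stop.
- 1,000 runs per setting; two-sided test at 5%.

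The planned model is final EPDS on module count plus the four covariates. The second model adds b. The landmark model takes women with at least 3 modules and adds b and e. Cells give the mean slope in EPDS points per module (negative = apparent benefit) and the percentage of runs that were significant.

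| n | r | g | planned | plus baseline EPDS | landmark |
|---|---|---|---|---|---|
| 278 | 0.5 | −0.5 | +0.093 (21.3%) | +0.093 (22.7%) | −0.002 (4.6%) |
| 278 | 0.5 | 0.5 | −0.092 (20.8%) | −0.090 (21.9%) | +0.006 (4.9%) |
| 278 | 0.5 | 0.8 | −0.131 (36.2%) | −0.131 (38.9%) | +0.006 (4.7%) |
| 278 | 0.7 | −0.5 | +0.101 (23.7%) | +0.102 (27.7%) | −0.004 (4.3%) |
| 278 | 0.7 | 0 | +0.002 (4.7%) | +0.001 (3.7%) | +0.003 (4.0%) |
| 278 | 0.7 | 0.25 | −0.049 (8.4%) | −0.050 (9.6%) | +0.002 (4.8%) |
| 278 | 0.7 | 0.5 | −0.103 (23.8%) | −0.104 (30.2%) | −0.001 (6.3%) |
| 278 | 0.7 | 0.8 | −0.159 (50.2%) | −0.160 (60.9%) | −0.001 (5.5%) |
| 139 | 0.7 | 0.5 | −0.096 (11.2%) | −0.100 (15.5%) | +0.008 (4.1%) |
| 139 | 0.7 | 0.8 | −0.162 (29.8%) | −0.162 (36.6%) | −0.003 (5.1%) |

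Over 10 modules the largest slope at n = 278 gives 10 × 0.159 = 1.6 points. The planned effect at the same SD is 0.3 × 5 = 1.5 points. The landmark works this well because, in this model, stopping depends on nothing unmeasured.

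**Calculation B: stronger dependence, on baseline severity as well.** Again no session effect; 200,000 women, EPDS SD 4, SD of individual spontaneous change 3. Sessions fall by the stated amounts per SD of baseline severity and per SD of early worsening.

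| dependence (baseline, early) | unadjusted | plus baseline EPDS | landmark | reduction |
|---|---|---|---|---|
| 0.5, 0.5 | −0.40 | −0.17 | −0.13 | 1 − 0.13/0.40 = 68% |
| 0.5, 1 | −0.54 | −0.33 | −0.26 | 1 − 0.26/0.54 = 52% |
| 1, 1 | −0.71 | −0.33 | −0.26 | 1 − 0.26/0.71 = 63% |

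**Reading the two together.** In both, the planned type of model gives a false slope whenever stopping depends on symptoms. They differ on the remedy. Baseline EPDS helps much in B, where stopping depends on baseline severity, and not at all in A, where it depends only on change. The landmark removes the bias in A and about half to two thirds of it in B.

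**The case against.** The covariate list is open. It gives examples and begins with sickness, which may be the woman's own. A reader might infer that symptom scores are excluded, but the text leaves them unnamed and does not rule them out. A full covariate list for an exploratory model may properly be left to the analysis plan. The as-treated analysis shows that the authors know the value of baseline endpoints as covariates, so it would be wrong to say that baseline variables enter the plan only as missing-data auxiliaries. All of this stands. It does not settle the point: the as-treated rule is not stated to govern this analysis, and baseline variables alone would not capture early course.

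A reader might also infer that the plan promises to show how many sessions are needed. It does not. It speaks of exploring relations and says that the exposure is not randomised.

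Nor do the documents support a dose scale of 0 to 6. Table 1 groups the 10 sessions under six headings but never calls those groups modules, and the abstract counts 10 modules. Defining the unit is a tidy-up.

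Finally, the size of the bias follows from assumed dependence parameters. It is zero when stopping is unrelated to symptoms. This stands too, and it limits the claim to what the slope can show.

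**Conclusion.** The point holds as a cheap improvement to an exploratory analysis. A regression on total self-selected module count, with no symptom score named among its covariates, can give a non-zero slope when sessions have no effect. Under the assumptions of calculation A with g from 0.25 to 0.8, the false slope is about 0.05 to 0.16 EPDS points per module, or 0.5 to 1.6 points over 10 modules. With 278 women, 8% to 50% of runs are then significant against a nominal 5%. Under the stronger assumptions of calculation B it is 0.40 to 0.71 per module. With g = −0.5, where improving women stop early, the sign reverses (about +0.1).

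The documents give none of these dependence parameters, so the range is illustrative and the larger figures are no forecast. A reader might infer that the analysis will show false benefit, or that the trial's main conclusion is at risk. Neither follows: the direction is not known in advance, and the primary comparison and sample size do not depend on this analysis.

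**What to change.** Keep the planned regression and add to it:
1. Define the exposure as logged completed sessions (0 to 10), counted up to the date of the endpoint assessment.
2. Add baseline EPDS, baseline stress and PATHEV to the listed covariates, in line with the as-treated analysis.
3. Add a supplementary landmark analysis among intervention-group women with a t0_1 assessment. Regress later EPDS on sessions completed from session 4 onward, adjusted for EPDS and stress at t0 and t0_1.
4. Report both as associations, not as the number of sessions needed.

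The cost is wording and one extra model, since every variable is already collected or logged. The landmark leaves out women who stop before session 4 and speaks only to later sessions, so it supplements the planned regression and does not replace it; early stoppers should be described separately. The t0_1 scores should not simply be entered into the full-count model: they follow the first sessions, may carry part of their effect, and may be absent for early stoppers. Adjusting for baseline EPDS alone may not remove the bias, and some may remain after the landmark.
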